## Abstract

**Background:**

It is increasingly acknowledged that clinical interventions for young persons with mental disorders need to optimize social, vocational and physical functioning, and take into account developmental needs, rather than focusing only on the traditional target of psychiatric symptom change. However, few interventions for youth presenting to mental health services offer a coherent rationale for multi-faceted approaches that efficiently address all these targets.

This trial uses two facilitated group therapy modules (social and physical activity) as a vehicle for promoting clinical, cognitive, social and vocational change. The modules are an adjunct to usual treatments offered to youth attending mental health services in Sydney, Australia.

**Methods/Design:**

The design is a 2-arm, parallel group cross-over, randomized clinical trial (RCT) that examines the efficacy of this adjunctive youth early intervention program (called “YES”) for improving social, vocational, mental and physical health functioning in a trans-diagnostic sample of 120 young persons aged 14–25 years who are currently receiving a range of “usual treatments” for clinically diagnosed anxiety, affective and/or psychotic disorders.

Individuals who provide written informed consent are offered 2 group therapy modules (each comprising 4 hours per week for 8 weeks) with a 3-week “pause” between modules. Randomization determines whether individuals commence with module A or module B. The sample will be assessed pre-randomization, and at week 1 and week 8 (after completion of the first module), and at week 11 (commencement of second module) and week 19 (completion of second module). Final follow–up is 1-year post trial entry.

**Discussion:**

If the findings of this exploratory trial demonstrate benefits in the target domains, then it will be important to extend the research by undertaking: (a) a comparison of the YES program to a control intervention in a randomized controlled trial, (b) an explanatory study of putative mediators of change, and (c) a multi-center trial with a number of trained therapists offering the group modules combined with a longer follow-up period.

**Trial registration:**

Australian New Zealand Controlled Trial Registration: ACTRN1262400175673, Date: 16 July 2015

## Background

Adolescence and young adulthood are stages of life characterized by marked emotional, cognitive and physical developments [1]. In addition, the mid-teens to mid-twenties represent the peak age range for the onset of all adult-type major mental disorders [2]. However, the longitudinal trajectory of the presenting syndrome is not always predictable. For example, a depressive episode may herald the beginning of a lifetime of recurrent depression, but it may also be a precursor of a future bipolar disorder or of psychosis. Alternatively, the depression may represent an isolated episode of ill-health that never recurs [3]. Not only do the early stages of a mental disorder present a complex clinical picture, but also the symptoms of any underlying illness often co-exist alongside other psychological difficulties that are indicative of age-appropriate emotional/developmental problems (anxieties regarding, e.g. acceptance by their peer group, school performance, body image, etc.) [1, 4, 5].

The entanglement of mental health and emotional/developmental problems is further complicated by the emergence of physical health issues. It is increasingly clear that these youth may already have “risky behaviors” that are potentially harmful to future health and wellbeing (e.g. use of nicotine and alcohol, sedentary lifestyle, etc.), precursor syndromes for medical problems (metabolic abnormalities, etc.) and/or other evidence of vulnerability for the development of persistent physical disorders (cardiovascular disease, type 2 diabetes, etc.) that are likely to become burdensome in middle and older age [5]. In summary, mental disorders in youth may have an uncertain longitudinal course and may be complicated by emotional development difficulties and/or by co-morbid physical disorders that predict later multi-system problems.

There is a growing body of research that indicates that due to this complex interplay between emotional developmental difficulties and/or co-morbid mental disorders or physical illness, young people are at risk of increasing levels of social and occupational disability [6–11]. This decline in functioning is marked by poor educational outcomes, limited employment choices, and estrangement from family and personnel connections. As such, young people can become marginalized from their immediate as well as their extended communities, exacerbating their levels of impairment [6–8].

For many decades, interventions for young people with mental disorders mirrored the treatments offered to older adults, with the main goal being the reduction of the acute clinical symptoms and not necessarily addressing their social and occupational decline [7]. There have been gradual modifications to the format of the treatments to try to adapt them to meet the needs of a younger population, but it is only relatively recently that service-delivery changes have become more widely established (e.g. early intervention in psychosis: EIP) [12]. The introduction of EIP helped to widen the focus of interventions to include functional outcomes such as educational attainment and social participation; and the latest expansion of service options, with shifts towards youth-friendly mental health services [13], has now helped to increase awareness of the need to address emotional developmental issues. However, relatively few programs have attempted to augment these approaches with interventions that target physical well-being (e.g. sleep regulation, reduced nicotine, alcohol and/or substance use), physical activity (e.g. exercise programs), improving “metabolic health” (e.g. raising awareness of and using interventions that target diet and body weight, stabilize blood sugars) and/or social recovery (e.g. returning to a state of well-being) [5, 7, 13]. Given the risk of recurrence or persistence of mental and physical disorders from adolescence into adulthood, (cardiovascular morbidity, type 2 diabetes, etc.) [5], it is worthwhile to try to develop multi-faceted clinical interventions that are accessible to the majority of youth presenting to clinical services, and target recovery and physical well-being, as well as reducing psychiatric symptoms; especially if the approaches potentially have high benefit-to-risk characteristics [5].

This study will primarily examine the short-term efficacy of two modules that together form a youth-focused group intervention (called YES). The two modules are: Social Participation (module A), which focuses on social participation, recovery and interpersonal skills; and Physical Well-being (module B), which concentrates on behavioral activity and physical health. The YES intervention (i.e. modules A and B) is offered as an adjunct to the usual treatments that young people receive in clinical care. The study will comprise a randomized clinical trial (RCT) and will primarily assess functional recovery (changes in vocational status) associated with participation in each module (either A or B); and whether the order in which the modules are offered (module A followed by B, or module B followed by A) has any differential benefits for participants. Secondary outcomes to be assessed will include measures of clinical improvement, level of engagement with the modules, and a pilot evaluation of any changes in physical health status (e.g. including smoking, anthropometric, laboratory measured parameters such as cholesterol levels and metabolic outcomes).

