### Measures

There are some resource constraints for this study; hence for the pilot RCT, we will use the clinical assessment of the case (including the DSM-IV diagnosis) provided from the details recorded at intake by the treating medical practitioner. Outcome measures will rely mainly on self-report ratings of progress and outcome, but the treating practitioner, (who is blind to the randomization sequence) will provide an observer rating for the key primary outcome measure (of social and occupational functioning).

We selected ten self-report ratings and one observer-rating scale to measure outcomes associated with each target domain. These research assessment tools are widely used in mental health research and were selected partly because many of them are regarded as “standard” measures of outcomes in community, clinical and research populations and/or they have been found to have acceptable reliability and validity across age groups [5, 10–12]. Furthermore, the BMRI clinical services use many of these ratings routinely. As described in our previous publications, the clinic provides ongoing training and supervision in the use of clinical assessment tools and observer rating scales to ensure inter-rater reliability and consistent use [15].

Measures of outcome are divided into primary and secondary ratings, and the time points for these assessments are shown in Table 1.

**Table 1 Tab1:** Schedule of enrollment, interventions and assessment time points

Phase	Pre-randomization		Post-randomization				Post-trial
Time point	Enrollment	Allocation	week 1	week 8	week 11	week 19	week 52 follow-up
Enrollment	x						
Clinical assessment (including DSM-IV diagnosis by treating medical practitioner)							
Eligibility screen	x						
Informed consent	x						
Randomization		x					
Allocates sequence of modules:							
AB or BA							
1^st^ Module							
2^nd^ Module							
Primary assessments:			x	x	x	x	x
Functioning - SOFAS and FAST							
Symptoms *-* SPHERE12			x	x	x	x	x
Disability *-* BDQ							
Self-esteem - RSEQ							
Vocational status:	x					x	x
Education, employment, receipt of benefits, etc.							
Engagement with intervention:				x		x	
Number of sessions attended							
Secondary assessments:			x	x	x	x	x
Levels of distress *-* K-10							
Social well-being *-* WHOQOL							
Physical health/Lifestyle:			x	x	x	x	x
Sleep profile - PSQI							
Exercise/Activity profile - IPAQ							
Tobacco and substance use *-* ASSIST							
Other measures:	x		x	x	x	x	x

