The routine intake assessment also collects data on educational or vocational status, and receipt of benefits. Again we will specifically ask clinicians to record this at selected time points throughout the course of the study.

For the purposes of the study, we will have access to records giving basic details of medication and/or other treatments received and will review these at the beginning of the study, at the end of the YES program, and again at the final follow-up. (However, this information will not be included in the formal analysis as resource constraints prevent us from collating information in sufficient detail to be able to interpret if findings are significant, e.g. differences dosages of medication prescribed, week-by-week medication changes, or levels of adherence, etc.)

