### Sample size/Power calculation

This feasibility study will allow us to undertake sample size calculations for future multi-center studies and inform the selection of outcome measures. There are no studies that have undertaken group interventions that target the same variables and outcomes specifically as this study and, most importantly, as both modules are deemed “active” interventions, we do not anticipate large between group differences associated with the modules. However, based on previous data from published clinical observational studies and controlled trials (that have estimated means scores on the SOFAS and FAST to be about 60–70 and 20–25 at baseline and clinically significant improvement to be associated with score changes of about 15–25 % over about 10–20 weeks), we have made a conservative estimate that each module can produce a statistically significant improvement in the scores (*p* < 0.05 with > 80 % power) on the 2 most important primary assessments: namely, the continuous measures of functioning (the FAST and SOFAS) of > 5 points between week 1 and week 9, and between week 11 and week 19 (we have not made any predictions associated to the 12-month follow-up).

Randomization of 120 individuals, with predicted retention of about 90–100 individuals at week 8 will give a sample size that is sufficient to detect clinically significant changes in functioning with medium to large effect sizes. Also, we predict this initial recruitment level would provide follow-up assessments on about 72–80 individuals at week 19 and about 66–70 individuals at 12 months.

Information on categorical outcomes (such as vocational status) is likely to be available on a larger sample, as it does not require the individual to participant in self-rated or observer-rated assessments, nor attendance for laboratory tests. Feedback is encouraged by all participants and is included as part of the week-to-week “summary/discussion” at the end of each group session. As such, whilst this information will be used for planning modifications to the programme, it is not being formally collated and analyzed.

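### The aims seek the change in vocational status with each module, but vocational status is recorded only at enrolment, week 19 and week 52, which leaves no randomised A-versus-B contrast on it; the aims also conflict with the analysis plan on the primary outcome

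*Protocol article*

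**What the plan says.** **Aim (Background, last paragraph).** The trial will "primarily assess functional recovery (changes in vocational status) associated with participation in each module", either A or B. A second question follows: "whether the order in which the modules are offered (module A followed by B, or module B followed by A) has any differential benefits".

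**How a module is isolated (Design).** The two groups are compared over weeks 1–8 and again over weeks 11–19. Weeks 1 and 8 are the start and end of the first module; weeks 11 and 19 are the start and end of the second.

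**Schedule (Table 1).** The columns run "Time point Enrollment Allocation week 1 week 8 week 11 week 19 week 52 follow-up". The vocational-status row, described as "Education, employment, receipt of benefits, etc", has marks under enrolment, week 19 and week 52, and blanks under allocation and weeks 1, 8 and 11. SOFAS and FAST are marked at weeks 1, 8, 11, 19 and 52.

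**Collection (end of Secondary outcome measures).** After noting that intake already captures vocational status, the text adds: "Again we will specifically ask clinicians to record this at selected time points throughout the course of the study". It names no time points.

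**Primary outcome elsewhere.** The numbered list of primary outcome measures has five scales (SOFAS, FAST, SPHERE 12, BDQ, RSEQ) and omits vocational status. The Sample size section bases its power statement on FAST and SOFAS. The Statistical analysis plan defines the primary outcome as change in FAST and SOFAS over weeks 1–8 and 11–19, and assigns vocational status to chi-squared tests and logistic regression with no time point stated.

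**The concern.** The design separates module A from module B only while the arms have received different modules, that is, after the first module ends and before the second begins. A status read at enrolment and next at week 19 misses that window. The Background nevertheless puts a module-specific question on exactly this outcome, and calls it primary.

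Two things are at stake. A question the article says it will answer has no randomised answer on the planned data, and an AB-versus-BA difference at week 19 could later be reported as though it were a module effect. In addition, the article gives two accounts of its primary outcome, which leaves room to choose between them after the results are known.

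**Working it through.** **Step 1. Read the row against the columns.** The seven columns are enrolment, allocation, week 1, week 8, week 11, week 19 and week 52. The vocational row is: mark, blank, blank, blank, blank, mark, mark. The empty cells survive in the table, so the marks fall unambiguously at enrolment, week 19 and week 52.

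**Step 2. Write the expected status in each arm.** Let μ₀, μ₈, μ₁₁ and μ₁₉ be the average over arms at each time. Let τ be the A-minus-B difference after one module, taken to persist through the pause. Let ω be the difference due to order once both modules have been given. Randomisation makes the arms equal at enrolment.

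| Time | A first | B first | Difference between arms |
|---|---|---|---|
| Enrolment | μ₀ | μ₀ | 0 |
| Week 8 | μ₈ + τ/2 | μ₈ − τ/2 | τ |
| Week 11 | μ₁₁ + τ/2 | μ₁₁ − τ/2 | τ |
| Week 19 | μ₁₉ + ω/2 | μ₁₉ − ω/2 | ω |

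**Step 3. Check what can be estimated.**

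- Enrolment and week 19 only: τ appears in no cell. The design matrix has rank 2 for 3 parameters (μ₀, μ₁₉, τ), or rank 3 for 4 when ω is added. The order effect is estimable and the module effect is not.
- Adding weeks 8 and 11: rank 5 for 5 parameters, or 6 for 6 with ω. The module effect becomes estimable.
- The week 52 reading comes after both modules, so it can inform order but not module.

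This result does not depend on the sample size, a variance or an assumed event rate.

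**Step 4. How informative would a week 8 record be?** The article gives no vocational rate and no allocation ratio, so this step rests on assumptions: equal arms, two-sided 5%, 80% power and a comparator rate of 20–50%. For n per arm, rates p₁ and p₂, and p̄ their mean:

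power = Φ{ [ |p₂ − p₁| − 1.96·√(2p̄(1−p̄)/n) ] / √[ (p₁(1−p₁) + p₂(1−p₂))/n ] }

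Example: n = 60, p₁ = 0.30, p₂ = 0.551, so p̄ = 0.4255. The two standard errors are √(2 × 0.4255 × 0.5745/60) = 0.0903 and √((0.2100 + 0.2474)/60) = 0.0873. Then (0.251 − 1.96 × 0.0903)/0.0873 = 0.85, and Φ(0.85) = 0.80.

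| n per arm | Basis | Detectable difference, comparator rate 20–50% |
|---|---|---|
| 60 | all 120 randomised | 24 to 25 points |
| 50 | 100 at week 8 | 26 to 28 points |
| 45 | 90 at week 8 | 28 to 29 points |

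The 90–100 is the article's retention forecast at week 8. It also says "Information on categorical outcomes (such as vocational status) is likely to be available on a larger sample", but does not tie this to week 8.

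**Step 5. Set the statements on the primary outcome side by side.** The Background says vocational status, by module. The list of primary outcome measures omits vocational status. The Sample size and Statistical analysis plan sections say FAST and SOFAS. The Background is the outlier.

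**The case against.** The strongest reply is that everything turns on one parenthesis in the Background. The operative sections make SOFAS and FAST primary, and both scales are read at the module boundaries, as the Design section requires. That stands. A reader might infer from the Background that the trial's primary module question cannot be answered; the documents do not support this, because it can be answered on SOFAS and FAST.

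A reader might also infer that week 8 is the only time the arms differ in the module received. It is not: week 11 is the start of the second module, so the arms still differ then. Vocational status is unmarked at both.

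Nor is every module-related analysis ruled out. The aim speaks of association with participation, and sessions attended are recorded at weeks 8 and 19, so attendance at each module could be related to vocational change. That analysis is possible but not randomised, and does not isolate a module's effect.

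Two further replies do not hold. The unspecified time points in the text on collection cannot be presumed to include week 8 when Table 1, the article's schedule of time points, lists three others. And this is not detail left to a fuller protocol or analysis plan: an explicit aim meets an explicit schedule, and no analysis method recovers a reading that the schedule does not collect.

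Finally, the article itself expects no large differences between the modules, so a week 8 contrast with the precision shown above would probably be inconclusive. That stands, and it is why the contrast should be secondary.

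**Conclusion.** The concern holds in a limited form. On the Table 1 schedule, no randomised A-versus-B contrast on vocational status can be estimated, so the module-specific aim in the Background cannot be met for that outcome. The AB-versus-BA comparison and change over the whole program can still be assessed. The module question is unaffected on SOFAS and FAST. Behind the schedule gap lies a naming conflict: the Background is at odds with the primary outcome list and the Statistical analysis plan on what is primary.

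The estimability result rests only on the Table 1 marks and on both arms being offered both modules by week 19. The precision figures of 24–29 points rest on assumed comparator rates, equal arms and 45 to 60 analysed per arm. Because the trial describes itself as exploratory and a feasibility study, and its operative primary outcomes are measured at the right times, this should be fixed but is not a fatal defect.

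**What to change.** 1. **In either case, reword the aim in the Background** so that SOFAS and FAST carry the primary module question, in line with the Sample size and Statistical analysis plan sections.
2. **Preferably, add vocational status to the week 8 column of Table 1**, and ideally to week 11, taken from clinic records. Compare A-first with B-first at week 8 by logistic regression adjusted for enrolment vocational status, and label the contrast secondary and probably imprecise.
3. **If no record is added**, limit vocational status to the order question and whole-program change, and drop the each-module wording for it.

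The rewording costs nothing in data collection. The extra record is one brief clinician entry per participant at one or two existing visits; the Sample size section notes that this item needs no participant assessment. Recruitment is already underway, so participants past week 8 could be completed only retrospectively from dated records, and any who cannot be completed would reduce precision further.

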## Methods

### Design

This is an un-blinded, two-arm, parallel group RCT with a cross-over design. The duration of the controlled phase of the RCT is 19 weeks. Participants will complete a pre-randomization assessment and after randomization to commence with module A or module B, they will complete further assessments at week1 and week8 (beginning and end of first module) and week11 and week19 (beginning and end of second module). The post-trial follow-up assessment will be undertaken 12 months after randomization.

The design will allow us to answer questions about the benefits of each module (comparison across groups between weeks 1–8; then comparison across weeks 11–19), and also whether benefits from or engagement with either module can be predicted by week 1 measures (e.g. are men more likely to engage with the module that targets activity whether this is offered for weeks 1–8 or for weeks 11–19? Do more individuals drop out in weeks 11–19 compared to weeks 1–8, no matter which module is being provided?).

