### Statistical analysis plan

All data are entered into and analyzed descriptively using SPSS, version 21 (SPSS Inc., Chicago, IL, USA). As this research was conducted in health service settings (with participants, clinicians and/or administration information being utilized\, there are variable rates of missing data, which will be taken into account in the analysis plan.

Primary analyses will be based on the intention-to-treat (ITT) sample: i.e. everyone who was randomized will be included in the analysis regardless of participation (full or partial or none) in the intervention groups. The primary outcome is the change in FAST (self-rated) and SOFAS (observer-rated) score pre-intervention to post intervention (e.g. between weeks 1–8 and then weeks 11–19). A preliminary analysis will be reported on week-8 outcomes once the target sample has completed this stage.

Further analyses will evaluate the scores at the end of the follow-up period and changes in secondary outcome measures. Categorical outcomes, such as vocational status will be examined using simple (chi-squared) and logistic regression models.

Mixed-model repeated measures analyses may be used for some analyses because of the ability of this approach to include participants with missing data without using discredited techniques such as last observation carried forward.

Additional analyses will include per-protocol analyses and statistical methods to explore factors that moderate outcomes, including attrition rates and, if appropriate, levels of presenting severity associated with significant social, clinical or functional improvement or change in vocational status.

Finally, some basic analyses will be undertaken of anthropometric and metabolic screening data. The latter will include a review of the uptake of these screening tests by study participants, and any barriers to this approach, as well as analysis of the findings. This pilot data will be used to inform power calculations for future studies.

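### The first scheduled SOFAS and FAST come at week 1, after randomisation, so the primary change score has no pre-randomisation baseline and people lost before week 1 have no change score

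*Protocol article*

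**What the plan says.** The Abstract states that "The sample will be assessed pre-randomization, and at week 1 and week 8". The Design section also mentions a pre-randomisation assessment and continues that "after randomization to commence with module A or module B, they will complete further assessments at week1 and week8". Design identifies these two visits as the "beginning and end of first module". Neither place says which instruments the pre-randomisation assessment contains.

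Table 1 does. The primary-assessments row, "Functioning - SOFAS and FAST", is empty under Enrollment and Allocation and marked at weeks 1, 8, 11, 19 and 52. The other rating scales (SPHERE-12, BDQ, RSEQ, K-10, WHOQOL, PSQI, IPAQ, ASSIST) follow the same pattern. The Enrollment column carries the clinical assessment, eligibility screen, consent, vocational status ("Education, employment, receipt of benefits, etc"), anthropometrics and blood tests.

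On blinding, Design says "This is an un-blinded, two-arm, parallel group RCT with a cross-over design". The Measures section adds that the treating practitioner, who rates SOFAS, does not know the randomised order. FAST is self-rated.

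The Statistical analysis plan section defines the primary outcome as change in FAST and SOFAS over weeks 1 to 8 and then weeks 11 to 19. It describes the primary analysis set as intention-to-treat: "everyone who was randomized will be included in the analysis regardless of participation (full or partial or none"). Mixed models are left as an option for part of the analyses.

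**The concern.** In a randomised comparison, the baseline is protected when it is measured before anyone knows the allocation. Here the first value of both key outcomes is taken afterwards. Two things can then differ between arms for reasons connected with allocation.

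- **The rating itself.** A participant pleased or disappointed with the module that comes first may complete FAST and the other self-report scales differently at week 1. Using that score as the start of a change score, or as a covariate, carries the difference into the comparison of module A with module B.
- **Who supplies a rating.** People may leave between allocation and week 1, possibly more often in one arm. They have no SOFAS or FAST, so no change score can be formed, and no earlier score exists to show whether they differed from those who stayed.

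The second route also sets the analysis-set promise against the assessment schedule: the plan includes everyone randomised but does not schedule the measurement needed to do so.

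**Working it through.** **1. Is the schedule read correctly?** The rows of Table 1 side by side:

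| Row | Enrollment | Allocation | Wk 1 | Wk 8 | Wk 11 | Wk 19 | Wk 52 |
|---|---|---|---|---|---|---|---|
| SOFAS, FAST | – | – | x | x | x | x | x |
| Vocational status | x | – | – | – | – | x | x |
| Anthropometrics | x | – | x | x | x | x | x |
| Blood tests | x | – | – | – | – | x | x |

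Three rows carry an Enrollment mark and fit the same seven columns, so the empty cell for SOFAS and FAST is not a reading error.

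**2. Is week 1 the baseline?** Yes. The primary outcome runs from week 1 to week 8 for the first module, the sample size section counts improvement from week 1, and Design uses week-1 measures as predictors.

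**3. How many people could lack a baseline?** The plan randomises 120 and predicts 90 to 100 retained at week 8.

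- Retention: 100/120 = 83.3%; 90/120 = 75.0%.
- Lost by week 8: 120 − 100 = 20 (16.7%) to 120 − 90 = 30 (25.0%).

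The plan does not split this loss into before and after week 1. If a share f is lost before week 1, 120 × (1 − f) people have a baseline:

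| f | With baseline | Without |
|---|---|---|
| 2% (assumed) | 117.6 | 2.4 |
| 5% (assumed) | 114 | 6 |
| 10% (assumed) | 108 | 12 |
| 16.7% to 25.0% (upper bound: all predicted loss before week 1) | 100 to 90 | 20 to 30 |

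Anyone who misses only the week-1 visit but returns later also lacks a baseline and would come on top of these numbers.

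**4. Who drops out of which analysis?**

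- Lost before week 1 and never rated later: no change score, and nothing to contribute to a mixed model of SOFAS or FAST.
- Missing at week 1 but rated at week 8 or later: no change score for the first module, but usable in a mixed model of the scores themselves.
- Rated at week 1, then lost before week 8: has a baseline and can enter a mixed model.

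The second and third groups are therefore retained only if the optional mixed model is used.

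**5. How would a shifted baseline act?** Suppose knowing the allocation shifts the mean week-1 score in one arm by δ and leaves week 8 unchanged. The difference between arms in mean change then moves by δ in size. If week 1 is a covariate with slope β, it moves by βδ. If the same shift persists at week 8, the change-score contrast does not move. The article gives nothing from which to estimate δ, so this step shows a mechanism and not a size.

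**The case against.** The best defence is that week 1 is the right starting point for what the trial is powered on. The sample size section concerns improvement within each module, and weeks 1 and 11 are matching start-of-module measures. A week-1 rating taken before the first session is still pre-treatment. This stands, and it is a reason to keep week 1. It does not help the comparison between arms that Design also promises, for which pre-treatment is not the same as pre-randomisation.

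Other points stand in part:

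- A reader might infer that both outcomes are rated with the allocation known. The documents do not support this for SOFAS, because its rater is stated to be blind to the order. The rating argument is confined to FAST and the other self-report scales; for SOFAS only selective loss remains.
- A reader might infer that every early drop-out falls outside the intention-to-treat analysis. That goes too far. The sentence is worded around attending groups, a non-attender could still be rated at week 1, and the plan says missing data will be taken into account. The conflict is limited to people without a week-1 score, and is complete only for those with no later score.
- A reader might divide an assumed FAST shift of 1 to 2 points by 5 and call it 20 to 40% of the target. The 5 points is a within-module change. The plan sets no 5-point difference between modules and expects no large one, so the percentage has no meaning for that contrast.
- Everyone is offered both modules and randomisation sets only the order, which weakens the disappointment argument without removing it.
- Many of the scales are in routine clinic use, so an intake score may exist for some people. Table 1 does not schedule it and the primary outcome does not use it.

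**Conclusion.** The point holds in limited form. On the published schedule the primary change score starts from a post-randomisation measurement in an un-blinded trial. That exposes the FAST and other self-report baselines to knowledge of the module order. It exposes SOFAS and FAST alike to selective loss before week 1.

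People lost before week 1 have no change score, which conflicts with including everyone randomised. Their number is not stated; the ceiling is 20 to 30 of 120, and it rests on the plan's own retention forecast and on the extreme assumption that all that loss comes before week 1. Neither the direction nor the size of any bias can be derived from the article. The case for acting is that the protection is cheap, not that a bias has been shown.

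**What to change.** - Add SOFAS and FAST to the Enrollment column of Table 1, completed before allocation, at the pre-randomisation assessment that already takes place.
- Keep the week-1 and week-11 measures. Moving the week-1 set to enrolment would remove the start-of-module measure that parallels week 11, and any change while waiting for the first group would count as a module effect in the first period only.
- Use the pre-randomisation value as the baseline covariate for the between-arm comparison.
- State that all randomised participants enter a longitudinal model of the scores, rather than leaving the mixed model optional.
- For people already recruited, use routine intake scores where they exist, and report how many have them.

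The cost is two short scales once per participant and a small amendment. Recruitment is under way, so some participants will lack a pre-randomisation FAST and the baseline will be of mixed origin. An enrolment score does not replace a missing outcome, but it allows those lost before week 1 to be compared with those who stayed.
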